### Measurement Instruments

#### Measures of Teamwork Quality

Both measures of teamwork quality are based on the TeamSTEPPS framework and include items related to the 5 facets of team structure, communication, leadership, situation monitoring, and mutual support. Details on the adaptation and validation process are provided in the corresponding section.

Objective teamwork will be measured through first-person video recordings of the VR sessions, which will be analyzed using the adapted version of the TPOT (vTPOT). This tool will evaluate observable behaviors and team interactions based on predefined teamwork criteria.

Subjective teamwork will be assessed using the adapted version of the T-TPQ completed by the participants after the first and third VR scenarios, focusing on their perceptions of teamwork quality.

#### Automatically Recorded Medical Performance Score

After each scenario, both team members can view and discuss the final evaluation together. All medical tasks specific to each scenario are assessed and it is recorded whether they were fully completed, partially completed, or not completed at all. The checklists for each scenario had been previously established by the authors based on guidelines from professional societies [23-25]. It was already ensured as part of a pilot study, that the automated final evaluation—in comparison with a manual checklist—accurately recorded all measures [10]. Importantly, when recording the tasks, the VR software does not differ whether they were carried out by medical or nursing staff. Based on that, a percentage score of medical performance for each team is generated.

### Ethical Considerations

The local institutional review and ethics board judged the project as not representing medical or epidemiological research on human participants and as such adopted a simplified assessment protocol. The project was approved without any reservation (proposal 20240422-01). Students will be informed about the study and their participation is voluntary. Written informed consent is obtained in printed form from all participants, who are also provided with information on data processing for the analysis and the publication of results. Contact details are supplied for participants wishing to withdraw their consent to data processing. The decision to participate or not has no consequences on the students’ academic progress. Survey data from the questionnaires are collected anonymously using the EvaSys platform. Data are processed and stored in accordance with local data protection laws. A €30 (approximately US $33.40) book voucher will be handed to the participants upon completion of day 3.

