A well-validated framework that includes educational content and both subjective and objective tools for assessing teamwork in physical simulations is the TeamSTEPPS framework [17]. In its current version (3.0), it covers 5 dimensions: team structure, communication, leadership, situation monitoring, and mutual support, and provides both subjective and objective evaluation metrics. The objective metric, the Team Performance Observation Tool (TPOT), has been significantly enhanced in terms of test-retest and interrater reliability through the inclusion of behavioral anchors compared to the original version [18]. In a recently published comparison of the most promising team performance assessment tools for evaluating longitudinal training, the TPOT was rated the most comprehensive tool and showed the second-best interrater reliability [19]. The associated questionnaire for subjective team member perceptions, the Teamwork Perceptions Questionnaire (T-TPQ), is also well-researched and validated [20]. While other assessment tools may outperform in specific criteria [12], the TeamSTEPPS concept is well suited for studies assessing comprehensive learning outcomes in simulations due to its alignment between teaching and assessment tools.

This study aims to adapt and validate objective and subjective assessment tools for the facets of teamwork that meet the requirements of VR-based environments, using the TeamSTEPPS measurement instruments. In the planned prospective study, these assessment tools will be used to measure the objective quality and the subjective perceptions of teamwork longitudinally (before, immediately after, and 1 week after completing a VR-based team training). In addition, the medical performance of the teams will be assessed based on the medical actions taken. The hypotheses derived from this are as follows:

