H1: A VR-adapted TPOT (vTPOT) supplemented with behavioral anchors demonstrates good item characteristics (concurrent validity, interrater reliability, and internal consistency) for the various facets of teamwork compared to the original version.H2: VR-based team training leads to a sustainable objective improvement in all facets of teamwork performance in interprofessional teams (as measured with the vTPOT).H3: VR-based team training leads to sustainable subjective improvement in all facets of teamwork perceptions in interprofessional teams (as measured with an adapted T-TPQ).H4: The increasing quality of teamwork is associated with an improvement in treatment quality, represented by the automatically recorded percentage of correctly performed medical actions.

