### Statistical Analysis

Test quality criteria of vTPOT will be assessed as follows: For concurrent validity, Pearson correlations will be calculated. Interrater reliability of the vTPOT will be calculated using Cohen Kappa to quantify the agreement between the assessments of the independent reviewers. Internal consistency of the vTPOT will be assessed by using Cronbach α. A value exceeding 0.7 will be considered acceptable, and greater than 0.8 as good. Considering the results of objective team performance, subjective teamwork perception, medical performance scores, and descriptive statistics including mean and SD will be calculated and presented in the format of mean and SD. Pearson correlations will be calculated to capture relationships between the results of different measurement instruments. The Shapiro-Wilk test is used to check for normal distribution. In case of a violation of the normality assumption, nonparametric tests (Wilcoxon rank test for group differences and Spearman test for correlations) are used. The calculations and generation of figures will be performed using GraphPad Prism (Version 10.1.2; GraphPad Software Inc).

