Despite these strengths, there are several limitations to consider. First, the absence of a control group limits our ability to definitively attribute improvements in teamwork to the VR-based training intervention alone. The pre-post design allows for intragroup comparisons, but the lack of a parallel group experiencing conventional training or no training reduces the robustness of our findings. In particular, regarding the subjectively perceived quality of teamwork, an anticipated treatment effect of uncertain magnitude could arise due to the lack of a control group. To mitigate this, we reassemble the teams for each session. While an effect due to mere repetition is also conceivable for the objective measurements of teamwork quality, it is less likely, as most TeamSTEPPS concepts (eg, check-backs, the Two-Challenge Rule) are unlikely to be learned intuitively. Moreover, the intervention (the training video on successful teamwork) is significantly shorter than typical training sessions from the TeamSTEPPS framework and may not achieve a sufficient effect. However, with regard to future application, it seemed important to find a training concept that could be applied both in academic studies and within the tightly scheduled clinical routine. In addition, the study is conducted at a single institution, which may restrict the generalizability of the results to other educational contexts or healthcare systems. Finally, another limitation stems from the voluntary nature of participant enrollment. It is possible that those opting to participate may already have a positive attitude toward teamwork or technology, potentially introducing a selection bias.

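### Questionnaires are described as anonymous with no linking code; as written, T-TPQ answers can be neither paired within student nor matched to session scores

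*Protocol article*

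**What the plan says.** In the protocol article, Ethical Considerations states how the questionnaires are gathered: "Survey data from the questionnaires are collected anonymously using the EvaSys platform". The article mentions no personal code, pseudonym, or team or session label on the forms.

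Other sections ask more of these data:

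- The Introduction says that "these assessment tools will be used to measure the objective quality and the subjective perceptions of teamwork longitudinally". H3 is that "VR-based team training leads to sustainable subjective improvement in all facets of teamwork perceptions in interprofessional teams".
- Measures of Teamwork Quality has the T-TPQ "completed by the participants after the first and third VR scenarios", that is, on day 1 and day 15.
- Strengths and Limitations states: "The pre-post design allows for intragroup comparisons".
- Statistical Analysis plans Pearson correlations to "capture relationships between the results of different measurement instruments". For non-normal data it names a "Wilcoxon rank test for group differences and Spearman test for correlations", without saying whether the comparison is paired.

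The vTPOT comes from video recordings of the sessions, and the medical performance score is produced by the VR software, one per team. Neither passes through the survey platform. Study Design re-randomizes the tandems at every session.

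**The concern.** Two links are needed to use the T-TPQ fully. One joins a student's day 1 form to the same student's day 15 form. Because tandems are reassembled each time, the student is the only unit followed across the study, so this is the only pairing available for H3. The other joins each form to the tandem and session it describes, so that perceived teamwork can be set against the vTPOT and the medical score of that session.

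Anonymous collection without any code removes both. The T-TPQ would then be two unlinked samples from the same people. Within-person change could not be analysed, and no T-TPQ result could be correlated with an objective one. A link missing at collection can rarely be restored later, and the Results section reports enrolment still ongoing in March 2025.

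**Working it through.** **The plan's own figure.** The sample size assumes a one-way ANOVA with 3 independent groups, 5% alpha, 80% power and a large effect. Taking large as f = 0.40 (an assumption; the article gives no value) and noncentrality N × f², the smallest total is N = 64, or 66 with equal groups of 22. Power at N = 65 is 81.2%. The stated figure of about 65 tandems is reproduced. It treats the timepoints as independent, so it does not depend on whether questionnaires are linked.

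**Inputs for H3.** n = 130 students at both visits (Sample Size Calculation); two-sided alpha 0.05. The within-person correlation r is not given, so 0.3, 0.5 and 0.7 are assumed. A true change of 0.3 SD is used for illustration. SDs are taken as equal at both visits, and clustering of two students in a tandem is ignored.

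**Standard errors, in SD units.**

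- Nominal SE in an unpaired test: √(2/n) = √(2/130) = 0.124.
- SE in a paired test: √(2(1 − r)/n), which gives √(1.4/130) = 0.104, √(1.0/130) = 0.088 and √(0.6/130) = 0.068.

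The second formula is also the true SE of the difference in means when the same students answer twice, linked or not. Losing the link leaves the estimate and its true precision as they are. The analyst, however, cannot estimate r and must use the larger nominal value.

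**True type I error of the unpaired test.** It is 2 × [1 − Φ(1.96/√(1 − r))].

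**Power of the unpaired test.** It rejects when the observed difference exceeds about 1.969 × 0.124 = 0.244 SD. For a true change of 0.3 SD, power is Φ((0.3 − 0.244)/true SE). At r = 0.5 this is Φ(0.056/0.088) = Φ(0.64), about 74%. Paired power is from the noncentral t distribution.

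| r (assumed) | Nominal SE, unpaired | SE, paired | True type I error, unpaired | Power, unpaired | Power, paired |
|---|---|---|---|---|---|
| 0.3 | 0.124 | 0.104 | 0.019 | 70% | 82% |
| 0.5 | 0.124 | 0.088 | 0.006 | 74% | 92% |
| 0.7 | 0.124 | 0.068 | 0.0003 | 79% | 99% |

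With the 28 teams reported in Results (56 students), the nominal SE is √(2/56) = 0.189, against √(1.0/56) = 0.134 paired at r = 0.5.

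**Which correlations are affected.**

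| Pair | Needs a survey form? | Without a session label |
|---|---|---|
| T-TPQ with vTPOT | Yes | Cannot be computed |
| T-TPQ with medical performance | Yes | Cannot be computed |
| vTPOT with medical performance (H4) | No | Unaffected |
| TPOT with vTPOT (validation) | No | Unaffected |

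**The case against.** The strongest reply is that a single word in an ethics section is being read too literally. The article does not exclude a self-generated code or a session number on the form, and a condensed article may leave such detail to the full protocol. This stands in part: it cannot be concluded that the forms are in fact unlinkable. But the article states a collection rule rather than staying silent, and that rule fits poorly with longitudinal measurement and intragroup comparison. If codes exist, the sentence misleads; if they do not, the T-TPQ data fall short of the stated aims.

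A reader might infer several stronger things that the documents do not support:

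- **That H3 becomes untestable.** No within-person test of H3 is named, the sample size assumes independent groups, and an unpaired comparison remains possible. With positive within-person correlation it errs towards missing an effect, not towards false positives.
- **That all cross-instrument correlations are lost.** Only those involving the T-TPQ are.
- **That the loss equals losing half the students.** At r = 0.5 the nominal variance is double the true one, but that is the precision the test reports, not the precision of the estimate.
- **That anonymity stops a tandem being followed from day 1 to day 15.** Re-randomization already does that, by design.
- **That the withdrawal option contradicts anonymity.** The article says: "Contact details are supplied for participants wishing to withdraw their consent to data processing". A truly anonymous form could not be found and removed, so the two sentences sit awkwardly together. The offer still has meaning for video and session data, and it does not promise retrieval of submitted forms.

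**Conclusion.** The point holds as a conditional one, confined to the subjective outcome. If questionnaires are collected as the article says, H3 loses its paired analysis and the planned correlations lose every pair that includes the T-TPQ. For H3 the cost is power: at 130 students and a change of 0.3 SD, 70% to 79% unpaired against 82% to 99% paired, over assumed correlations of 0.3 to 0.7. H4, the vTPOT validation and the sample size figure are untouched.

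The sizes rest on assumed correlations, an illustrative change, complete data at both visits and no clustering within tandems. The direction holds for any positive within-person correlation at the power levels considered here. This is a should-fix: the remedy is cheap and the loss is hard to reverse, but a valid if weaker test of H3 survives.

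**What to change.** In Ethical Considerations, replace the word anonymously by pseudonymously and state how forms are linked. Put on each EvaSys form a study code or a self-generated personal code, the session number and a tandem-session ID. Keep any key to identities away from the analyst. In Statistical Analysis, state that H3 is analysed as within-person change from day 1 to day 15.

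If codes are already in use, correcting the sentence is enough. Forms already collected without a code should be declared as entering only as unlinked data.

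The cost is one or two fields on the form, a short notice to the ethics board and an update of the participant information. The downside is slightly less privacy than full anonymity. The tandem-session ID alone, without a personal code, would restore the T-TPQ correlations but not the paired test of H3.

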### Statistical Analysis

Test quality criteria of vTPOT will be assessed as follows: For concurrent validity, Pearson correlations will be calculated. Interrater reliability of the vTPOT will be calculated using Cohen Kappa to quantify the agreement between the assessments of the independent reviewers. Internal consistency of the vTPOT will be assessed by using Cronbach α. A value exceeding 0.7 will be considered acceptable, and greater than 0.8 as good. Considering the results of objective team performance, subjective teamwork perception, medical performance scores, and descriptive statistics including mean and SD will be calculated and presented in the format of mean and SD. Pearson correlations will be calculated to capture relationships between the results of different measurement instruments. The Shapiro-Wilk test is used to check for normal distribution. In case of a violation of the normality assumption, nonparametric tests (Wilcoxon rank test for group differences and Spearman test for correlations) are used. The calculations and generation of figures will be performed using GraphPad Prism (Version 10.1.2; GraphPad Software Inc).

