### Study Design

A prospective preintervention-postintervention study will be conducted between May 2024 and June 2025. Teams consisting of 1 nursing and 1 medical student will complete 3 different interprofessional VR-based scenarios on 3 dates. These teams will be newly randomized for each session.

Three scenarios, each lasting about 30 minutes, will be completed by all participants in random order on different dates: (1) esophageal variceal bleeding due to ethyl-toxic liver cirrhosis, (2) exacerbated chronic obstructive pulmonary disease, and (3) tachycardic atrial fibrillation due to complicated urinary tract infection. The contents of the scenarios and indicated medical actions are listed in Table S1 in Multimedia Appendix 1 and were already described in detail elsewhere [16,22]. Participants can communicate via voice-over IP and interact with each other through avatars during the scenarios (eg, handing over equipment or demonstrating findings on a screen). The type and order of medical actions and teamwork elements are not predetermined and can be independently structured by the team members (eg, briefing and mid-discussion). After the scenario, a detailed guideline-based evaluation of the medical actions and an overview of the physiological course of the disease can serve as the basis for debriefing.

On the first date (day 1), informed consent will be obtained. A tutorial will follow to familiarize participants with VR hardware and software. The first scenario will be completed without specific prior team training (pre-test). On the second date (day 8), a training video on successful teamwork including practical recommendations will be shown (approximately 30 min). The content of the training video is based on the official TeamSTEPPS guidelines [17] and has been adapted by the authors of the study to fit the specific context (limited time and VR setting). In addition, video examples were shown to demonstrate how certain team interactions (particularly for performing “Check-Backs,” “Huddles,” giving feedback, and applying the “Two-Challenge Rule”) can be implemented in VR. Then, the second scenario will be completed (post test). A total of 7 days later (day 15), without additional training, the third and final scenario will be completed (retention test). Figure 2 provides an overview of the study design and data collection.

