#### Sample Size Calculation

Since the team tandems are reassembled in a new, randomized form at each session a sample size estimation for 3 repeated measures timepoints could not be computed. Instead, we had to assume 3 independent groups. A between-groups ANOVA with an α level of 5%, a power of 80%, and assuming a large effect size, indicated that approximately 65 team tandems would be required, resulting in a total of 130 participants.

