## Results

This study received ethics approval in April 2024. As of May 2024, the enrollment of participants is ongoing and currently (March 2025) has 28 enrolled interprofessional teams. Data collection and analysis will be complete in December 2025.

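### The only stated analysis that could test H4 is an unadjusted correlation, which, if sessions are pooled, can show a teamwork–treatment link produced by a shared session trend

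*Protocol article*

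**What the plan says.** The fourth hypothesis in the Introduction reads: "The increasing quality of teamwork is associated with an improvement in treatment quality", with treatment quality taken as the automatically recorded percentage of correct medical actions.

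The Statistical Analysis section does not name H4. Its one provision for links between measures is: "Pearson correlations will be calculated to capture relationships between the results of different measurement instruments". If normality fails, the fallback is "Wilcoxon rank test for group differences and Spearman test for correlations". No adjustment for session, scenario or repeated participation is given, and the section does not say whether the three sessions are pooled.

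Three design features bear on this:

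- Study Design: "These teams will be newly randomized for each session". Each participant completes all three scenarios, in random order, over three dates.
- Automatically Recorded Medical Performance Score: "The checklists for each scenario had been previously established by the authors". The score is a percentage of scenario-specific tasks, and both team members can see and discuss the evaluation after each scenario.
- H2 predicts that vTPOT rises after the day 8 training video.

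**The concern.** H4 speaks of an increase in one quantity going with an improvement in another. Because every team is new at every session, no team-level change can be computed for either. Two readings of the stated correlation remain.

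- **Pooled over sessions.** vTPOT is expected to rise after day 8. The medical score may rise too, through familiarity with the software and the evaluation shown after each scenario. Two measures that both step up between sessions correlate positively even if, within a session, teams with better teamwork treat no better than the others.
- **Session by session.** This removes the session trend but says nothing about increase, so it does not address H4 as worded.

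Scenario is a second possible source of bias under either reading, since scenarios are mixed within each session. It distorts the correlation only if it shifts both vTPOT and the medical score. Finally, each student contributes to three team-sessions, so the points are not independent as the test assumes.

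At stake is whether a significant correlation may be reported as support for H4, the one hypothesis that ties teamwork to care.

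**Working it through.** **Inputs from the document.** Three sessions; about 65 tandems planned (Sample Size Calculation), so 65 × 3 = 195 team-sessions; "currently (March 2025) has 28 enrolled interprofessional teams" (Results), so 28 × 3 = 84 if recruitment ended there.

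**The plan's own figure.** The sample size rests on "A between-groups ANOVA with an α level of 5%, a power of 80%, and assuming a large effect size" and concludes that "approximately 65 team tandems would be required". No numerical effect size is given. For three independent groups, noncentral-F power with f = 0.40 needs 64 in total (66 with equal groups); f = 0.25 needs 158 and f = 0.50 needs 42. So f = 0.40 reproduces the stated figure. The calculation does not concern H4; it only shows what size of effect was probably meant by large.

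**Assumptions.** Session means are 0, d, d in SD units, and the two measures are independent within each session (no true link). The SD of these means is f = d√2/3, so f = 0.40 corresponds to d = 0.40 × 3/√2 = 0.85.

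**Spurious correlation.** With steps giving f₁ (vTPOT) and f₂ (medical score):

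r = f₁f₂ / √[(1 + f₁²)(1 + f₂²)]

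For equal steps of 0.85 SD this is 0.16/1.16 = 0.138. The rate of significant positive results is approximately Φ(atanh(r)·√(n − 3) − 1.96), with √192 = 13.86 for n = 195.

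| vTPOT step (SD) | Medical step (SD) | Expected r | Positive false positives, formula | Simulation |
|---|---|---|---|---|
| 0.85 | 0.85 | 0.138 | 49% | 46–49% |
| 0.85 | 0.50 | 0.085 | 22% | 21–22% |
| 0.85 | 0.30 | 0.052 | 11% | 11% |
| 0.85 | 0.20 | 0.035 | 7% | 7% |
| 0.85 | 0 | 0 | 2.5% | 2.4% |
| 0.30 | 0.30 | 0.020 | 4.6% | 4.5% |

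With 84 team-sessions and 0.85 SD in both, √81 = 9 and the formula gives Φ(0.139 × 9 − 1.96) = 24%; simulation also gives about 24%.

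**Other settings, by simulation with no true link (two-sided rejection, nominal 5%, 65 teams per session).**

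- Spearman under the 0.85 SD session step in both measures: 46.6%. The fallback is no protection.
- Pearson within a single session under the same trend: 5.0%. The session problem disappears if sessions are not pooled.
- Scenario shifting both measures in the same direction at f = 0.40: 49.4% pooled, 19.6% within one session. In opposite directions, the mean r is −0.14.
- Scenario shifting the medical score alone, by ±0.5 SD: r = 0.00 and 5.1%; by ±1 SD: 4.8%. No bias.
- Partial correlation adjusted for session and scenario: 4.3% to 5.5% in every setting tried.

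These simulations do not include the repeated appearance of students, so no size is attached to that part. The crossed random-intercept model was not simulated either; only the fixed-effect adjustment was.

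**The case against.** The strongest reply is that the protocol never says sessions are pooled, and that a condensed article may leave this to a fuller plan. A reader might infer that H4 as planned carries a false-positive rate near one half. The document does not support that. The figure needs pooling, and it needs a step of 0.85 SD in both measures. The sample size section says only that the effect is large and names no outcome, nothing assumes such a step in the medical score, and Strengths and Limitations warns that the short video may have too little effect even on teamwork. This stands, and it is why a range is given.

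A reader might also infer that different checklists per scenario are enough to confound the correlation. They are not. They may shift the medical score, but vTPOT would have to shift too, and no section says that it does. This also stands.

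Third, H4 claims association, not that better teamwork causes better care, and adjusting for session changes the question by removing between-session gains. That is true. However, the document concedes that there is no control group, so those gains cannot be separated from practice and feedback. What can be estimated is association within session and scenario.

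Last, H4 is one of four hypotheses and the sample size does not rest on it. That lowers the severity but does not remove the point: the method is named, it is unadjusted, and neither reading of it tests H4 soundly.

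**Conclusion.** The point holds in a conditional form. The stated correlation does not fit H4, because team change scores do not exist and per-session correlations do not address increase. If pooled, it absorbs any session trend common to vTPOT and the medical score. The distortion ranges from none (no step in the medical score) through modest (11% against 2.5% when vTPOT steps 0.85 SD and the medical score 0.3 SD) to serious (46–49% with equal steps of 0.85 SD), all at 195 team-sessions. Small shared trends of 0.3 SD barely matter. Every step size is an assumption. Scenario bias is possible but conditional on scenario moving both measures. Dependence from repeated students is real but not quantified here. Severity: should be fixed.

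**What to change.** State H4 at the level of the team-session. Make the primary H4 result the vTPOT coefficient, with confidence interval, from a model of the medical score on vTPOT, session and scenario, with crossed random intercepts for the medical and the nursing student. At minimum, report a partial correlation adjusted for session and scenario. Show the unadjusted correlation as descriptive only.

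Say plainly that this estimates association within session and scenario, since gains between sessions cannot be separated from practice without a control group.

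Include T-TPQ only if responses can be linked to teams: Ethical Considerations says the questionnaires are anonymous, and Measures of Teamwork Quality collects them after the first and third scenarios only, so the second session has no value.

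The cost is a change of analysis wording. vTPOT, medical score, session and scenario are already part of the data collection. The random intercepts also need each student to be identifiable across team-sessions. The reported association may be smaller, and software other than the package named in Statistical Analysis may be needed.
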